#### **Secondary hypotheses:**

- 1) Depressed patients show significantly higher inflammatory parameters and lower vagus function (logRSA) at the start of the study compared to healthy control subjects.
- 2) The vagus function (logRSA) and inflammatory parameters (hsCRP, IL-6) of depressed patients and healthy control subjects do not differ significantly after 3 months of intervention.
- 3) Vagus function correlates with depression scores, inflammatory parameters, oxytocin, and gut microbiota (in diversity, composition, and function) in both healthy control subjects and depressed patients.

- 4) Stool samples from the intervention group show a significantly higher proportion of short-chain fatty acids after the intervention.
- 5) The content of short-chain fatty acids in stool correlates with vagus function in healthy control subjects and in depressed patients.
- 6) Vagus nerve function correlates negatively with depression scores, sleep quality scores, subjective stress experience, and the diversity and composition of the gut microbiome.

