## **Abstract**

### **Justification:**

Depression is one of the most common and serious illnesses worldwide and has a significant negative impact on patients' quality of life and ability to work. Patients with depression exhibit changes in the gut microbiome and its metabolites, which in turn influence the gut-brain axis as a bidirectional communication system. A key component of this axis is the vagus nerve, which transmits information from the internal organs in the periphery to the central nervous system. Studies have shown that the function of the vagus nerve is impaired in patients with depression. At the same time, depressed patients often have a pro-inflammatory status, which is linked to the function of the vagus nerve in influencing the immune response. Animal models have shown that vagal afferents transmit information from intestinal bacteria directly to the central nervous system and can thus induce both anxious and depressive behaviour. Stimulation of the vagus nerve (which is currently used clinically as an invasive procedure for treatment-resistant depression) has been shown to improve depression and alleviate (neuro)inflammation. A pilot study from our working group has shown that the diversity of the gut microbiome in women correlates with the function of the vagus nerve ([name]/Oberascher et al., 2020, in prep).

**Relevance:** To date, no research has been conducted into whether and to what extent probiotics can influence the function of the vagus nerve. This new mechanism could be used to specifically alter the function of the vagus nerve with probiotics and provide a rationale for add-on therapy with probiotics ("psychobiotics").

**Design:** This monocentric study will investigate the effect of a multi-strain probiotic on vagus nerve function in 40 depressed patients and 40 healthy control subjects in a placebo-controlled setting. The study participants will receive either a probiotic or a placebo for 3 months, and the function of the vagus nerve will be determined at 4 time points using a portable ECG, which will be worn for 24 hours. In addition, inflammation markers (hs-CRP, IL-6) and the gut microbiome were determined using 16S sequencing. This is the first study worldwide to investigate the effects of a multistrain probiotic on the vagus nerve in depressed patients compared to healthy control subjects. The results of this study could contribute to a better understanding of the basis of probiotic effects on mental processes.

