## 6. Statistics

### 6.1 Randomisation

The study design results in 4 groups:

- **Depressed patients Probiotics/placebo**
- **Healthy subjects: probiotics/placebo**

The subjects are using computer-assisted **4-person block randomisation** (randomisation.com).

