## 6.2 Considerations regarding the number of cases

This project is a pilot study. To the best of our knowledge, probiotic effects on vagus function in depressed patients have never been investigated before. A power analysis was performed using G\*Power 3.1.(29). In the F-tests category, the

"Repeated Measures ANOVA within-between interaction" was selected as the procedure. With a low effect size of 0.2, alpha 0.05 and 95% power, a total of 80 participants (20 participants per group) is required for 4 groups (healthy subjects: probiotic/placebo; depressed patients: probiotic/placebo).

[figure not shown]

Figure 3: Sample size calculation with G\*Power

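### Secondary hypothesis 2 takes a non-significant patient-control difference at 3 months as its success criterion, names no arm and has no placebo contrast, so meeting it shows neither similarity nor a probiotic effect

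*Protocol*

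**What the plan says.** Protocol section 3.2 lists six secondary hypotheses. The first expects patients to have higher inflammatory markers and lower logRSA than controls at the start. The second says that logRSA, hsCRP and IL-6 "of depressed patients and healthy control subjects do not differ significantly after 3 months of intervention". It names no treatment arm and does not mention placebo.

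Elsewhere in the protocol:

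- Section 6.1 (Randomisation): "The study design results in 4 groups", that is, patients and healthy subjects each split into probiotic and placebo.
- Abstract: "40 depressed patients and 40 healthy control subjects in a placebo-controlled setting".
- Section 6.2: "With a low effect size of 0.2, alpha 0.05 and 95% power", giving "a total of 80 participants (20 participants per group) is required for 4 groups". The procedure is the interaction test of a repeated-measures ANOVA.
- Primary hypotheses: these do compare probiotic with placebo on the same markers, but at 4 weeks.
- Section 2: patients are recruited while being treated for depression as inpatients.
- Per-protocol analysis: this is the primary evaluation concept, and cases without the data for the primary endpoints are excluded from it.

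**The concern.** A hypothesis worded as "do not differ significantly" makes a failed significance test the success criterion. A test can fail because the groups are alike or because the data are too imprecise to separate them, and the wording does not distinguish the two. Incentives also run the wrong way, since every dropout or per-protocol exclusion makes the hypothesis easier to support.

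The second problem is attribution. Even a true closing of the gap would not point to the probiotic, because the comparison is between diagnoses and not between probiotic and placebo. The patients are under treatment throughout the early part of the study and would be expected to change anyway.

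At stake is the 3-month conclusion. Hypotheses 1 and 2 together read as a gap before and no gap after. A report that follows them as written could present a persisting gap as closed, or credit the probiotic with a change that the placebo patients also showed.

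**Working it through.** **1. The plan's own figure.** Section 6.2 gives effect size f = 0.2, alpha 0.05, power 95% and 4 groups. The number of measurements is taken as 4 (Abstract). The within-subject correlation (0.5) and sphericity (epsilon = 1) are assumed, because the software figure is not shown.

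- Noncentrality = f² × N × m / (1 − rho) = 0.04 × 80 × 4 / 0.5 = 25.6
- df = (4 − 1)(4 − 1) = 9 and (80 − 4)(4 − 1) = 228
- Power = 0.960, and N = 80 is the required total

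So 80 is reproduced, but for detecting an interaction. Nothing in it was sized to show that two groups are alike.

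**2. Chance that one marker is non-significant although a gap remains.** Two-sided two-sample t test at alpha 0.05, noncentrality d × √(n/2), df = 2n − 2. For d = 0.5 the noncentrality is 0.5 × √20 = 2.24 at 40 vs 40 and 0.5 × √10 = 1.58 at 20 vs 20. The gaps d are assumptions, because the documents state none.

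| True gap (SD) | 40 vs 40 (all patients, all controls) | 20 vs 20 (probiotic arms only) |
|---|---|---|
| 0.2 | 86% | 91% |
| 0.3 | 74% | 85% |
| 0.5 | 40% | 66% |
| 0.8 | 6% | 31% |

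95% CI half-width = t(0.975, 2n − 2) × √(2/n): 0.445 SD at 40 vs 40 and 0.640 SD at 20 vs 20.

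**3. All three markers.** If logRSA, hsCRP and IL-6 must all be non-significant, with equal gaps and independent markers, the single-marker chance is cubed:

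- 40 vs 40: 0.737³ = 0.40 at 0.3 SD; 0.402³ = 0.065 at 0.5 SD
- 20 vs 20: 0.848³ = 0.61 at 0.3 SD; 0.662³ = 0.29 at 0.5 SD

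Positive correlation between the markers moves these towards the single-marker values, so the two sets bracket the answer.

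**4. Effect of losses.** With an assumed 20% loss (32 vs 32), the single-marker chance at 0.5 SD rises from 40% to 50%.

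**5. What the result says about the probiotic.** Two assumed scenarios:

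- Usual care closes the gap and the probiotic does nothing. The true difference is 0, and each marker is non-significant in 95% of trials under either reading.
- The probiotic improves patients and controls equally, by 0.3 SD each, which fits the primary hypothesis, and the starting gap is 0.5 SD. The gap stays 0.5 SD, and one marker is non-significant in 40% (40 vs 40) or 66% (20 vs 20), exactly as with no probiotic effect.

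An inert product can thus meet the hypothesis, and an effective one need not change its chance of being met.

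**6. Threshold.** The data-analysis section prints a significance threshold of 0.5, against 0.05 in section 6.2. That is a separate inconsistency, and 0.05 is used here. Taken literally, 0.5 would make non-significance harder to reach: truly equal groups would pass only 50% of the time per marker.

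**The case against.** Several stronger readings are tempting, and the documents do not support them.

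- **That the plan pools probiotic and placebo.** The hypothesis names no arm, and section 6.1 lists four separate groups without collapsing them. Secondary hypothesis 4 and section 6.3 use the word intervention for the probiotic arm as opposed to placebo, so a probiotic-only reading is open. What can be said is that the arm is unspecified. The narrower reading does not rescue the hypothesis: it still lacks a placebo contrast, and it halves the sample.
- **That the plan claims proof of normalisation.** It uses neither word. The inference is a fair one from hypotheses 1 and 2 read together, but it remains an inference, and a misreport is a risk rather than something the protocol states.
- **That the criterion is easily met in general.** It is for small and moderate gaps. At 0.8 SD with 40 vs 40, one marker is missed only 6% of the time, and requiring all three markers lowers the chances further.

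It is also fair to say that this is one of six secondary hypotheses in a self-described pilot, that the placebo comparison sits in the primary hypothesis, and that a margin or model term may be left to an analysis plan that is not shown. The absence of a margin is therefore not the point. The success criterion is in the protocol sentence itself, and an analysis plan that follows it inherits the flaw.

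**Conclusion.** The concern holds in a limited form. As worded, secondary hypothesis 2 takes a failed test as support for similarity and contains no placebo contrast. Meeting it shows neither that patients and controls are alike nor that the probiotic made them so, and the attribution point stands under both readings of the arm.

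The size depends on a gap the documents do not give. For moderate gaps of 0.3 to 0.5 SD, false reassurance on one marker runs from 74% down to 40% at 40 vs 40, and from 85% down to 66% at 20 vs 20. If all three independent markers are required, the ranges are 40% down to about 6-7%, and 61% down to 29%. For gaps near 0.8 SD at 40 vs 40 the problem is small. These figures assume alpha 0.05, equal variances and no losses.

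The primary hypothesis is unaffected. The wording should be changed before analysis, because it bears on the 3-month conclusion.

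**What to change.** Restate secondary hypothesis 2 as follows:

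- Name the arms being compared.
- Ask whether the patient-control gap at 3 months changes more under probiotic than under placebo (diagnosis × treatment term, baseline-adjusted). This tests a differential effect only: an equal benefit in both diagnoses leaves it at zero, so it does not replace the probiotic-placebo contrast.
- Report the patient-control difference at 3 months with its 95% CI, labelled descriptive, and state that non-significance will not be read as similarity.
- If a similarity claim is wanted, require the CI (90% for two one-sided tests at 5%) to lie within a margin set and justified beforehand.

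The change needs wording only and no new data. Its cost is that a clear answer is unlikely at this size:

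- **Interaction:** the standard error with 20 per cell is √(4/20) = 0.447 SD, so the unadjusted 95% CI half-width is 1.99 × 0.447 = about 0.9 SD. A 0.5 SD narrowing would be detected roughly 20% of the time, or about 25% after baseline adjustment if the correlation with baseline is 0.5 (assumed).
- **Two one-sided tests, true difference zero:** power at 20 vs 20 is about 3% for a 0.5 SD margin and 60% for 0.8 SD. At 40 vs 40 it is 44% and 94%, but that comparison mixes the arms. For 80% power, a 0.5 SD margin would need 69 per compared group.

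The most practical course at N = 80 is the descriptive estimate with its interval, with inconclusive accepted in advance as the likely result. The present wording hides that uncertainty.

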### **3.1 Inclusion and exclusion criteria**

**Inclusion criteria** for this study are: informed consent, diagnosis of depression according to ICD-10, age between 18 and 65 years.

**Exclusion criteria** are: suicidal tendencies, lack of consent or capacity to consent, known cardiovascular disease, pregnancy, breastfeeding, pronounced dependence on alcohol or psychotropic substances (benzodiazepines, morphine), other severe mental or organic diseases (epilepsy, brain tumours, trauma, recent major surgery), tumour diseases, dementia (Mini Mental Score <20), severe autoimmune diseases or immunosuppression (lupus erythematosus, HIV, multiple sclerosis), antibiotic therapy in the last month, laxative abuse, acute

infections, diarrhoea, gastrointestinal surgery (except appendectomy). Participants should not have taken probiotics in the last 6 months. Furthermore, they should not consume any additional dietary supplements or probiotics during the study period. The additional intake of antibiotics or prebiotic supplements is also considered an exclusion criterion.

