##### H1:

A 4-week intake of a multi-species probiotic shows a significant increase in vagal function (measured by HRV, log RSA) and a significant decrease in inflammation parameters (IL-6, hsCRP) in subjects with depression and in healthy control subjects compared to placebo treatment.

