## 5. Methods

### 5.1 Intervention with multispecies probiotic

The multistrain probiotic and placebo used are provided by the Allergosan Institute. This is a commercially available dietary supplement called OMNi-BiOTiC® -SR, which contains 9 bacterial strains (*Bifidobacterium bifidum* W23, *Bifidobacterium lactis* W51, *Bifidobacterium lactis* W52, *Lactobacillus acidophilus* W22, *Lactobacillus casei* W56, *Lactobacillus paracasei* W20, *Lactobacillus plantarum* W62, *Lactobacillus salivarius* W24, *Lactococcus lactis* W19) with at least 7.5 trillion microorganisms per serving (=3g).

The placebo preparation will have the same colour, consistency and taste as the probiotic product. The matrix of the product contains corn starch, maltodextrin, inulin, potassium chloride, magnesium sulphate, fructooligosaccharides, amylases and manganese sulphate. Patients and healthy controls receive OMNi-Biotic SR after it has been dissolved in water and the activation time of 10 minutes has been observed. For inpatients, the study preparation is prepared daily at 7:00 a.m. by study staff and given to inpatients before breakfast and in the evening every day until discharge. After discharge, patients continue to take the preparation twice daily at home on their own. The entire study team is blinded.

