#### **5.4 Microbiome analysis**

One gram of stool is collected at three test times and immediately stored in an -80°C freezer for further analysis. The microbiome is evaluated using Illumina MiSeq according to a previously published procedure (Klymiuk et al., 2017) [32]. FastQ files are used for data analysis. Quantitative Insights Into Microbial Ecology (QIIME II) is used on the MedUni Graz galaxy server to evaluate the gut microbiome (galaxy.medunigraz.at). Depending on financial resources, the metabolome (from stool) will also be analysed.

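### Secondary hypothesis 4 names no placebo comparator, so a before-after rise in stool short-chain fatty acids in the probiotic arm alone would satisfy its wording

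*Protocol*

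**What the plan says.** Protocol section 3.2, secondary hypothesis 4: "Stool samples from the intervention group show a significantly higher proportion of short-chain fatty acids after the intervention". One arm and a time phrase are given; neither baseline nor placebo is named as the reference.

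Other parts of the protocol do give a reference:
- H1 in section 3.2 is stated "in subjects with depression and in healthy control subjects compared to placebo treatment".
- The abstract describes the study as run "in 40 depressed patients and 40 healthy control subjects in a placebo-controlled setting".
- Section 6.3 compares alpha diversity between the intervention and placebo groups.
- Section 6.2 bases the sample size on a within-between interaction.

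The following passages bear on what else could move stool short-chain fatty acids:
- Section 5.1, on the product: "The matrix of the product contains corn starch, maltodextrin, inulin, potassium chloride, magnesium sulphate, fructooligosaccharides, amylases and manganese sulphate".
- Section 5.1, on the placebo: "The placebo preparation will have the same colour, consistency and taste as the probiotic product". Whether it has the same matrix is not stated expressly.
- Section 5.1, on setting: the preparation is "given to inpatients before breakfast and in the evening every day until discharge" and is then taken at home.
- Section 3.1: "The additional intake of antibiotics or prebiotic supplements is also considered an exclusion criterion".
- Section 5.2 records diet by 24-hour recall; no section sets a controlled diet.

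On the assay, section 5.4 says only: "Depending on financial resources, the metabolome (from stool) will also be analysed". Stool is collected at three test times.

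**The concern.** A hypothesis about a treatment effect in a randomised, placebo-controlled study should be met only by a difference between the randomised arms. Hypothesis 4 is looser. Read literally, it is met when stool from the probiotic arm has more short-chain fatty acids at the end than at the start, whatever happens on placebo.

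The protocol's own text offers reasons for such a rise other than the nine strains. The matrix includes inulin and fructooligosaccharides. Depressed patients move from hospital to home during treatment. Diet is recorded but not fixed. A change from any of these could be reported as confirming hypothesis 4 without any difference from placebo. Hypothesis 5 then relates short-chain fatty acids to vagus function, so a spurious result on hypothesis 4 would colour how that correlation is read.

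Because the sentence leaves the comparator open, it could also be settled after the data are seen.

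**Working it through.** **1. The plan's own figure.** Hypothesis 4 has no figure of its own. The only one nearby is the total of 80 in section 6.2 (effect size 0.2, alpha 0.05, power 95%, 4 groups). For the within-between interaction, λ = f²·N·m/(1−ρ), df1 = (k−1)(m−1) and df2 = (N−k)(m−1). With k = 4, m = 4 (the abstract's four time points), f = 0.2 and ρ = 0.5:
- λ = 0.04 × 80 × 4 / 0.5 = 25.6
- df1 = 3 × 3 = 9; df2 = 76 × 3 = 228
- power = 0.960, and the required N is 80

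The stated N reproduces, but ρ = 0.5 is an assumption because the readable text does not give it. This is background only. It shows that the design was sized for a comparison of change between groups.

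**2. The wording side by side.**

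| Statement | Reference named |
|---|---|
| H0 and H1, section 3.2 | placebo |
| Secondary hypothesis 1 | healthy controls |
| Alpha diversity, section 6.3 | placebo |
| Secondary hypothesis 4 | none |

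**3. What the two readings do when the bacteria have no effect.** Inputs:
- n = 40 per arm (20 depressed and 20 healthy, section 6.2)
- two-sided alpha of 0.05
- a shift d in units of the SD of within-person change, **assumed** at 0.2 to 0.8 because the protocol gives no short-chain fatty acid mean, SD or expected change

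Within the probiotic arm, the chance of a significant rise is 1 − F(t; n−1, d√n), where F is the noncentral t distribution function and t is the 0.975 quantile of the central t with n−1 degrees of freedom. For n = 40, d√n = 1.26, 1.90, 3.16 and 5.06 at the four shifts.

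Against placebo, with the same shift in both arms, the shift cancels. The chance of a significant result in favour of probiotic is 0.05/2 = 0.025.

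| Shared shift d | Within arm, n = 40 | Within arm, n = 20 | Versus placebo |
|---|---|---|---|
| 0.2 | 0.23 | 0.13 | 0.025 |
| 0.3 | 0.46 | 0.25 | 0.025 |
| 0.5 | 0.87 | 0.56 | 0.025 |
| 0.8 | >0.99 | 0.92 | 0.025 |

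A normal approximation gives similar values for n = 40 (0.24, 0.48, 0.89, >0.99).

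**4. Shift in depressed patients only (discharge).** With 20 of the 40 in each arm shifted, 40,000 simulated trials give a within-arm probability of 0.15, 0.32 and 0.64 at d = 0.3, 0.5 and 0.8. The comparison with placebo gives about 0.02 throughout.

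**5. Shift in the probiotic arm only (matrix absent from placebo).** The two-sample test has noncentrality d√(n/2) with 78 degrees of freedom. It is significant with probability 0.14, 0.26, 0.60 and 0.94 at d = 0.2, 0.3, 0.5 and 0.8. In that case a placebo comparison does not separate the strains from the matrix.

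**The case against.** The strongest reply is that no within-arm test is stated. Section 6.3 uses the term intervention group in contrast to placebo, so hypothesis 4 can be read as higher than placebo at the end of the intervention. The design is placebo-controlled, and the test for a secondary hypothesis is commonly left to an analysis plan, which is not at hand. This stands in part. A reader might infer that the protocol plans to discard the randomisation for this endpoint, and the text does not support that. What remains is that the hypothesis itself is fixed in the protocol, and its most literal reading does not need placebo.

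A reader might also infer that a rise is to be expected even if the strains do nothing. The protocol does not show that. It gives no amounts of inulin or fructooligosaccharides and no short-chain fatty acid data, and it does not say that these ingredients raise short-chain fatty acids. That step is an assumption, so such a rise is possible and no more. Excluding prebiotic supplements in section 3.1 is an eligibility rule; it does not by itself show that the protocol treats them as a confounder.

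Discharge cannot affect the healthy controls, who are half of each arm by design. Applying a discharge shift to all 40 would overstate the effect: 0.87 instead of 0.32 at 0.5 SD.

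Nor do the documents show that the placebo lacks the matrix. The matrix sentence follows directly on the placebo sentence and may describe a shared carrier. Likewise, hypothesis 4 speaks of a proportion and hypothesis 5 of content. This loose wording is worth tidying but is not an error on its own.

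**Conclusion.** The point holds as a missing comparator. Hypothesis 4 omits the placebo reference that H1 carries, and a rise in the probiotic arm alone would satisfy it as written.

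The probabilities in the working illustrate how far the two readings can diverge; they do not predict what this trial will show. They depend on the assumed shift, on a simple t-test of change and on all 40 participants per arm contributing data. The contrast with 0.025 further assumes that the shift is the same in both arms, which for a matrix effect requires the placebo to carry the same matrix.

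Severity is low to moderate. The hypothesis is secondary, section 6.2 calls the project a pilot study, and the only stool metabolite assay mentioned depends on funding.

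**What to change.** Reword secondary hypothesis 4 along these lines: *The change in stool short-chain fatty acids from baseline to 3 months is greater with probiotic than with placebo.* Use one named measure of short-chain fatty acids in hypotheses 4 and 5.

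If the placebo does not contain the same inulin and fructooligosaccharide matrix, attribute any difference to the whole product and not to the strains. A sentence in section 5.1 on what the placebo contains would settle which applies.

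The cost is a change of wording. The visit schedule and stool collection make no distinction between arms, so no new sampling is needed. The statistical price is power. If a true change of 0.5 SD occurred only in the probiotic arm, the within-arm test with n = 40 would detect it with probability 0.87 and the two-sample comparison of change with 0.60. That loss is the price of a result that can be attributed to the randomised treatment.

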Heart rate variability (HRV) measures cardiac autonomic regulation and describes the degree of fluctuation in heartbeats (R-R intervals) that can be derived from an electrocardiogram. These intervals are not constant and vary with each heartbeat. Basically, a higher HRV means better vagus nerve function and better health (10). Reduced vagus nerve function is associated with a reduction in HRV and a monotonous regularity of heart rate (22). A meta-analysis of HRV in depressed patients showed that they had reduced HRV indices compared to healthy control subjects and that depression correlated negatively with HRV (23). HRV is associated with inflammatory markers (CRP and IL-6). For example, Jarczok et al. showed that vagus nerve function could predict CRP levels (10, 23).

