## 6.1 Data analysis and evaluation

The data obtained will be analysed using IBM SPSS, version 27. A descriptive data description (mean, standard deviation, percentile rank) will be provided. Correlations between variables will be calculated using Pearson's correlation coefficient or Spearman's correlation coefficient, depending on the distribution. Error probabilities below  $p < 0.5$  are considered statistically significant. Microbiome analyses are performed in R (version 3.6) and Rstudio (version 1.2.1555) (R-doundation, Vienna, Austria), with visualisations using the ggplot2 library.

Both an intention-to-treat and a per-protocol analysis are performed.

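### Secondary hypothesis 6 names no group and the plan gives only simple correlations, so the expected patient–control difference alone could produce the predicted negative coefficient, chiefly for sleep and stress scores

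*Protocol*

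**What the plan says.** Section 3.2 of the protocol lists three secondary hypotheses about correlations with vagus function.

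- Hypothesis 3 covers depression scores, inflammatory parameters, oxytocin and gut microbiota, and ends "in both healthy control subjects and depressed patients".
- Hypothesis 5 says that stool short-chain fatty acids "correlates with vagus function in healthy control subjects and in depressed patients".
- Hypothesis 6 says: "Vagus nerve function correlates negatively with depression scores, sleep quality scores, subjective stress experience, and the diversity and composition of the gut microbiome". It names no group, and it alone covers sleep quality and subjective stress.

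The method is in section 6.1 (Data analysis and evaluation): "Correlations between variables will be calculated using Pearson's correlation coefficient or Spearman's correlation coefficient, depending on the distribution". That sentence serves all three hypotheses and mentions neither stratification nor adjustment for diagnosis.

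The groups are expected to differ in vagus function. Hypothesis 1 states: "Depressed patients show significantly higher inflammatory parameters and lower vagus function (logRSA) at the start of the study compared to healthy control subjects". Section 1 cites a meta-analysis of depressed patients in which "they had reduced HRV indices compared to healthy control subjects and that depression correlated negatively with HRV". Per the Abstract and section 2, the sample is 40 patients, recruited as inpatients, and 40 healthy controls.

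**The concern.** When two groups differ in the mean of both variables, a coefficient over the combined sample contains the between-group difference as well as any relation among people within a group. Here the groups are expected to differ in logRSA. Depression scores will differ because patients are selected on a depression diagnosis, and sleep and stress scores plausibly differ too. Lower vagus function together with worse scores in patients pushes the pooled coefficient below zero, the direction that hypothesis 6 predicts. Confirming hypothesis 1 would then push hypothesis 6 towards confirmation without adding independent evidence.

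At stake is interpretation. A finding that vagus function tracks sleep or stress would be read as support for the vagal mechanism that the study sets out to explore, when it might only restate the case-control contrast. The protocol also states the relation with depression scores and microbiota twice: in hypothesis 3 with both groups named and no direction, and in hypothesis 6 with a direction and no group. A within-group and a pooled correlation are different quantities and can disagree.

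**Working it through.** **The plan's own figure.** The protocol gives no figure for the correlation hypotheses. Its only calculation (section 6.2) is for the repeated-measures interaction. With f = 0.2, alpha 0.05, 4 groups, 4 measurements and assumed G*Power defaults (correlation 0.5, sphericity 1), N = 80 gives power 0.9595, so the stated 80 reproduces. It does not bear on hypothesis 6.

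**Inputs from the protocol.** 40 patients and 40 controls; logRSA expected to be lower in patients; simple Pearson or Spearman coefficient.

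**Assumed inputs.** The protocol gives no group gaps. I take a logRSA gap d₁ of 0.2 to 0.8 SD (patients lower) and a score gap d₂ of 1 to 3 SD (patients higher, with higher meaning worse). Both variables are normal within group, with zero correlation inside each group.

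**Threshold.** Section 6.1 prints "Error probabilities below $p < 0.5$ are considered statistically significant", while section 6.2 uses alpha 0.05. I use 0.05.

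**Coefficient induced by group alone.** With equal groups (p = q = 0.5, pq = 0.25):

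r = −d₁·d₂·0.25 / √[(1 + 0.25·d₁²)(1 + 0.25·d₂²)]

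- d₁ = 0.5, d₂ = 3: −0.375 / √(1.0625 × 3.25) = −0.375 / 1.858 = −0.20
- d₁ = 0.5, d₂ = 1: −0.125 / √(1.0625 × 1.25) = −0.125 / 1.152 = −0.11
- d₁ = 0.2, d₂ = 1: −0.05 / √(1.01 × 1.25) = −0.05 / 1.124 = −0.04
- d₁ = 0.8, d₂ = 3: −0.60 / √(1.16 × 3.25) = −0.60 / 1.942 = −0.31

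**How often the pooled Pearson test reaches p < 0.05** (20,000 simulated trials of 40 + 40 per cell; induced r in brackets):

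| logRSA gap (SD) | score gap 1 SD | score gap 2 SD | score gap 3 SD |
|---|---|---|---|
| 0.2 | 7% (−0.04) | 10% (−0.07) | 11% (−0.08) |
| 0.3 | 9% (−0.07) | 16% (−0.11) | 19% (−0.12) |
| 0.5 | 16% (−0.11) | 34% (−0.17) | 44% (−0.20) |
| 0.8 | 31% (−0.17) | 68% (−0.26) | 83% (−0.31) |

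Nearly all these rejections are in the negative direction. In a separate run of 4,000 trials at 0.5 and 3 SD, Spearman gave 44%, so switching coefficient does not help.

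**After adjustment.** With group means removed (77 degrees of freedom), the rejection rate is 4.7% to 5.2% in every cell.

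**Scope.** The calculation fits scores on which patients sit higher. For microbiota the protocol does not state the direction of the group gap, so the induced sign is not known there.

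**The case against.** The strongest reply is that pooling is inferred. The protocol nowhere says that hypothesis 6 will be tested on all 80 people as one sample, the method sentence is generic, and a statistical analysis plan not seen here could stratify or adjust. It can be added that hypotheses 3 and 5 have no stratified method either, so hypothesis 6 might be meant the same way. It stands that pooling is not stated, and a reader who infers that the protocol commits to a pooled test goes too far. It does not remove the point: of three neighbouring hypotheses two name the groups and one does not, and the only method given offers no protection against the group effect.

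Four narrower objections stand.

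- Hypothesis 3 already gives a group-named form for depression scores and microbiota.
- A reader might infer that all the scores form two clusters by design. That is reasonable for depression scores. Section 3.1 sets no sleep or stress criterion, and section 2 admits mild to severe episodes, so for those two scores separation is an assumption.
- The gaps are not in the documents. At the low end the excess is slight, about 7% against 5%.
- An association across the full range of severity is a legitimate question, and adjusting a depression score for a depression diagnosis removes part of that range. The answer is to label the pooled coefficient for what it is, not to forbid it.

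**Conclusion.** The point holds in limited form. As worded, hypothesis 6 can be confirmed by the case-control difference that hypothesis 1 already predicts, with no association inside either group. The problem is full for sleep quality and subjective stress and partial for depression scores and microbiota. Its size depends on assumed gaps: about 16% false support at 0.5 and 1 SD, about 44% at 0.5 and 3 SD. Here false support means support for a within-group relation when that relation is zero.

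It would be too strong to say that the trial will report a spurious mechanism. The protocol does not fix a pooled test, and a real within-group association is not excluded. This is one of six secondary hypotheses in a self-described pilot, and it touches neither the primary endpoints nor the sample size. A correction is still worthwhile because it is cheap and the conclusion at risk is a mechanistic one.

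**What to change.** Add to section 6.1 that hypothesis 6 is tested as a correlation adjusted for diagnosis group (partial Pearson or Spearman) in all 80 people, using one visit per person, such as baseline. Show the coefficient within patients and within controls alongside. Label any unadjusted pooled coefficient as descriptive, because it includes the case-control difference. Align the wording of hypothesis 6 with hypotheses 3 and 5.

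The cost is a sentence or two of text and one degree of freedom (77 instead of 78), with no new data and no change to conduct. Precision within each group of 40 is lower. By Fisher's z, 80% power at two-sided 0.05 needs z = (1.96 + 0.84)/√37 = 0.46, so r of about 0.43 within a group, against 2.80/√76 = 0.32, so r of about 0.31, for the adjusted coefficient in all 80. For depression scores, adjustment also narrows the severity range under study. The adjusted coefficient should therefore be the test and the within-group values supporting detail.
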